#### Activity Trackers

Activity trackers (Nokia Go wristband, Nokia France, Issy-les-Moulineaux, France) are given to all study participants. Patients are instructed to wear the device every day for the duration of the 6-month intervention. In addition, patients receive real-time feedback on their number of steps per day. Recommendations are to achieve 5000-10,000 steps a day depending on patients’ ability and comorbidities. For a patient who reaches 10,000 steps per day, we will advise her to maintain her goal. For a patient who is not able to achieve 5000 steps a day, we will gradually increase her objective. The goal is adjusted regularly throughout the 6-month intervention period. The instructor has access to the data pertaining to the number of steps per day and can modify the daily steps goal directly in the app or by a phone call to the patients during meetings.

Data are collected by regular transfer to the wearable activity tracker mobile phone app (Nokia Health Mate) available on a mobile phone or Tablet PC. Patients can use the mobile phone app to follow their number of steps per day represented by a graph. After receiving the wearable activity tracker, patients are called on days 7 and 14 to ensure the proper use of the device and answer any questions. Personalized objectives might be redefined to increase their daily physical activity. For patients without a mobile phone, data are collected during the 6-month intervention when visiting the hospital for a consultation every week or 2 weeks. Instructors might use the activity tracker interface to monitor change over time and to adapt to physical activity recommendations. At the end of the 6-month intervention, patients can keep the activity tracker to continue their efforts.

### Data Collection

Table 1 provides the complete data collection schedule in this study.

All assessments are recorded at the baseline and the end of the 6-month physical activity program (M6) by the instructor, as seen in Figure 1.

#### Demographic and Clinical Data

Demographic and clinical data, including date of birth, age at diagnosis, living situation, employment status, hormonal status, tumor histology, personal history of breast cancer, sites of metastases, and current treatment, are collected at the baseline. The Response Evaluation Criteria In Solid Tumors (RECIST) is used to assess the tumor progression between the diagnosis and the end of the physical activity program [36]. All clinical data are extracted from patients’ electronic medical records.

#### Body Composition and Anthropometrics

The standing height (cm), body weight (kg), waist (cm), and hip (cm) circumferences are measured using standardized procedures. The waist circumference is measured midway between the last floating rib and the iliac crest. The hip circumference is measured at the tip of the pubis. The body mass index is calculated as the body weight in kilograms divided by the square of the height in meters.

#### Physical Activity Fitness and Sedentary Behavior

Cardiorespiratory fitness is measured by evaluating the peak oxygen consumption during the 6-minute walk test (6MWT) [37,38]. Patients are asked to perform the maximum walk shuttle distance on 30-meter-long flat corridors in 6 minutes. During this test, the oxygen consumption, carbon dioxide production, heart rate, and oxygen arterial saturation are continuously recorded using a portable respiratory gas analyzer (MetaMax 3b; Cortex Biophysik, Leipzig, Germany). In addition, the perception of the difficulty during 6MWT is evaluated at the end of the test using the Borg Rating of Perceived Exertion questionnaire [39].

Then, prehensile and grip strength is measured using a hand dynamometry (Jamar Plus Digital Hand Dynamometer; Patterson Medical, Huthwaite, United Kingdom), which is a validated index of the elbow extension strength [40]. Moreover, patients are asked to squeeze the handgrip as strongly as possible for 5 seconds to obtain the maximal force. Of note, two measures are performed on each hand, and the best performance is registered.

The maximum isometric strength of quadriceps extension is measured using a back-leg dynamometer (DFS II Series Digital; Force Gauges Chatillon, Largo, FL, USA). Patients are asked to sit on a chair with the knee articulation at 90°, arms crossed on the chest, and the dynamometer attached to the ankle. At the signal of the instructor, patients must try to extend the leg as strongly as possible in 3 seconds. Only the dominant leg is tested twice, and the best performance is obtained.

The International Physical Activity Questionnaire (IPAQ) [41] is used to measure the self-reported physical activity. IPAQ (long form) is a validated self-administered physical activity questionnaire with 31 items and covers 4 activity domains, work-related physical activity, transportation physical activity, domestic physical activity, and recreational physical activity [41]. IPAQ gives specific scores in the metabolic equivalent of task (MET)-minutes/week for walking, moderate-intensity, and vigorous-intensity activity within each of the work, transportation, domestic chores and gardening (yard), and leisure-time domains. Questions are coded and converted in MET per minute and per week according to the Compendium of Physical Activities [42] by multiplying the number of METs by the duration and frequency of the activity. Then, the total physical activity score for each intensity is obtained by adding the score for this intensity in each domain and by adding the number of MET-minutes per week at each intensity.

**Table 1 table1:** The data collection schedule for the Advanced stage Breast cancer Lifestyle and Exercise Trial.

Assessments		Time		
		Patients’ recruitment	Day 1: Baseline	Month 6: End of the study
**Clinical data (patient record)**				
	Date of birth		✓	
	Age at diagnosis		✓	
	Employment status		✓	✓
	Hormonal receptor status		✓	
	Personal history of breast cancer		✓	
	Metastasis localization		✓	✓
	Current treatment		✓	✓
	Tumor histology		✓	
	Disease progression (Response Evaluation Criteria In Solid Tumors)		✓	✓
Demographic data			✓	✓
Anthropometrics^a^			✓	✓
**Physical fitness**				
	6-minute Walk Test with oxygen consumption		✓	✓
	Upper limb strength: handgrip		✓	✓
	Maximum isometric strength of quadriceps extension		✓	✓
	International Physical Activity Questionnaire (long form)		✓	✓
	Sedentary behavior: Marshall Questionnaire		✓	✓
	Steps per day: Activity tracker^b^			✓
**Psychological questionnaires**				
	Quality of life: Cancer Quality Of Life Questionnaire, breast cancer module		✓	✓
	Fatigue: Piper Fatigue Scale		✓	✓
	Physical activity preferences, facilitators, and barriers	✓	✓	✓
	Incentive effect of activity tracker			✓
	Social deprivation: EPICES (Evaluation of Deprivation and Inequalities in Health Examination Centres) score	✓	✓	✓
**Other**				
	Reason for refusal	✓		

^a^Height, weight, waist-to-hip circumference, and body mass index.

^b^During 6 months.

Next, the global score of physical activity is divided into 3 categories commonly used by physical activity guidelines (<600 MET-minutes/week is equivalent to low physical activity; between 600 and 3000 MET-minutes/week is equivalent to moderate physical activity; and >3000 corresponds to high physical activity [43]). Furthermore, the sedentary time in minutes per week is obtained by adding the weekday sitting time in minutes for 5 weekdays, and the weekend sitting time in minutes for 2 days.

#### Patient-Reported Outcomes

The quality of life is measured with the European Organization for Research and Treatment of Cancer Quality Of Life Questionnaire (QLQ-C30) and its specific module for breast cancer (BR-23) [44]. QLQ-C30 is a 30-item self-administered questionnaire that evaluates 5 functioning domains (physical, role, emotional, cognitive, and social), a global quality of life domain, 3 symptom domains (pain, fatigue, and nausea), and 6 single items (dyspnea, insomnia, anorexia, diarrhea, constipation, and financial impact). Each item is associated with a score ranging from 0 to 100. For the functioning and global scales, a higher score corresponds to a better functioning level. The specific module for breast cancer (BR-23) gathers data about perceived body image, sexual functioning, sex enjoyment, arm symptoms, breast symptoms, and systemic therapy side effects.

Fatigue is assessed with the revised Piper Fatigue Scale [45,46], which is a 22-item self-reported questionnaire with 4 subscales, behavioral and severity, affective, sensory, and cognitive and mood. All these items together produce a score for total fatigue defining categories as follows: no fatigue (score=0), mild fatigue (score 1-3), moderate fatigue (score 4-6), and severe fatigue (score 7-10).

The social deprivation is assessed using the EPICES (Evaluation of Deprivation and Inequalities in Health Examination Centres) score [47,48]. The score is computed by adding each question coefficient to intercept whenever the answer is “yes.” The score ranges from 0 to 100 with the threshold for deprivation at 30, and higher scores indicate greater deprivation levels.

#### Determinants of Physical Activity

Preferences, facilitators, and barriers are evaluated with the translated version of a specific questionnaire developed by Vallance et al [49]; this questionnaire includes questions regarding the interest and willingness of patients with metastatic breast cancer to participate in a physical activity program designed for patients with metastatic breast cancer. In addition, it includes questions on their interest and preferences for physical activity counseling and specific aspects of these programs, including how, where, and when they would be interested in these physical activity programs as well as the type of intervention that would be most amenable for them.

#### Biological Data

A 7-mL blood sample is collected at the baseline (D1) and at the end of the study after 6 months (M6). The sample is centrifuged within half an hour after drawing and kept at 4°C before and during centrifugation. The plasma is distributed into cryotube aliquots of 1 mL and buffy coat in a single 1-mL cryotube; these cryotubes are frozen and stored at −80°C at the center and used for the analyses of oxidative stress and antioxidant biomarkers. Superoxide dismutase, catalase, glutathione peroxidase enzymatic activities, and markers of DNA oxidation (8-hydroxy-2'-deoxyguanosine), prostaglandins oxidation (8-Iso Prostaglandin F_2α__)_ are measured in the plasma [50]. Furthermore, levels of circulating growth factors, cytokines, neutrophils, monocytes, and natural killer cells are assessed as previously described [51].

### Statistical Analysis

#### Sample Size

The sample size was defined empirically to explore the feasibility of the program according to the enrollment potential in the study center. Because the main objective of the ABLE Trial was to assess the feasibility of a physical activity intervention in women with metastatic breast cancer, without major regard for the efficiency, no formal calculation was performed. Given that 200 patients are treated annually for metastatic breast cancer in the Center Léon Bérard and that 60% of patients are expected to survive for at least 6 months, with a projected acceptance rate of 50%, the pilot study will aim to recruit 60 patients within 9 months.

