**Methods:**

We plan to conduct a single-center, single-arm trial with 60 patients who are newly diagnosed with metastatic breast cancer. Patients will receive an unsupervised and personalized 6-month physical activity program that includes an activity tracker Nokia Go and is based on the physical activity recommendation. Patients will be encouraged to accumulate at least 150 minutes per week of moderate-to-vigorous intensity physical activity. Baseline and 6-month assessments will include anthropometric measures, functional tests (eg, 6-minute walk test and upper and lower limb strength), blood draws, patient-reported surveys (eg, quality of life and fatigue), and clinical markers of tumor progression (eg, Response Evaluation Criteria In Solid Tumors criteria).

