### Study Population

The inclusion criteria for this study are as follows: (1) female; (2) aged 18-78 years; (3) newly diagnosed with primary or secondary metastatic breast cancer histologically confirmed (ie, within the last 3 months) and treated in a cancer center by chemotherapy or radiotherapy or hormonal therapy or targeted therapy; (4) Eastern Cooperative Oncology Group Performance status <2; (5) able to speak and understand French and able to complete questionnaires and follow instructions in French; and (6) valid health insurance affiliation. For patients willing to participate in the study, confirmation from their treating oncologist of no contraindications to physical activity is required.

The exclusion criteria for this study are as follows: untreated brain metastases; pregnancy; and contraindications to physical activity (eg, uncontrolled hypertension, cardiac disease). All patients must sign an informed consent form.

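### The accrual projection applies survival and acceptance to 200 treated patients a year with no factor for the entry criteria, so its base is broader than the eligible population

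*Protocol article*

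**What the plan says.** The Sample Size section of the protocol article states that "The sample size was defined empirically to explore the feasibility of the program according to the enrollment potential in the study center", and that no formal calculation was made. The numerical support is a chain of three factors:

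- base: "Given that 200 patients are treated annually for metastatic breast cancer in the Center Léon Bérard";
- survival: "60% of patients are expected to survive for at least 6 months";
- acceptance: "with a projected acceptance rate of 50" percent.

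The result is that "the pilot study will aim to recruit 60 patients within 9 months".

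The Study Population section limits entry to women "newly diagnosed with primary or secondary metastatic breast cancer histologically confirmed (ie, within the last 3 months"), with "Eastern Cooperative Oncology Group Performance status <2". It adds limits on age (18 to 78), French language and health insurance, and excludes untreated brain metastases, pregnancy and contraindications to physical activity. The Methods part of the abstract also describes the sample as "60 patients who are newly diagnosed with metastatic breast cancer".

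The Statistical Methods section defines the acceptance proportion, which the trial will estimate, with eligible patients as its denominator.

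**The concern.** The projection and the entry criteria describe different populations. The projection starts from everyone treated for metastatic disease at the center in a year. The criteria admit a subset: recent diagnosis, good performance status and several further conditions. Nothing in the chain takes the first group down to the second. The 50% acceptance rate is therefore applied to a pool that has not been reduced to eligible women, although the article's own definition of acceptance uses that smaller group.

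This matters because the center's capacity to enroll is the only basis given for the figure of 60. The Discussion says the trial's results will help to design a multicenter randomized trial, for which the number of eligible women per site is a basic input. The issue concerns accrual planning, not inference.

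**Working it through.** **Inputs.** From Sample Size: base 200 a year, survival 0.60, acceptance 0.50, period 9 months, target 60. From Study Population: diagnosis within the last 3 months, ECOG below 2, and the other criteria. Not given in the article: the eligible share e of the 200. It is treated as unknown and shown over a range.

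**Step 1. Reproduce the plan's figure.** 200 × 0.60 × 0.50 = 60. The three stated factors use up the whole figure, so the implied eligible share is 100%. The base is annual, so this 60 is a 12-month number.

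**Step 2. Scale to the stated period.** 60 × 9/12 = 45. With an eligible share, nine-month accrual is 45e.

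**Step 3. Allow for the look-back.** A woman diagnosed up to 3 months before opening can still enter. A 9-month window could therefore draw on at most 9 + 3 = 12 months of diagnoses, which gives 60 × 12/12 = 60, or 60e. This is an upper limit, and the article does not offer it as its rationale.

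**Step 4. Drop the survival factor.** Surviving 6 months is not an entry criterion, so for recruitment the factor can be left out.

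- Annual: 200 × 0.50 = 100.
- Nine months: 100 × 9/12 = 75, so 75e.
- With the full look-back: 100 × 12/12 = 100, so 100e.

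**Step 5. Eligible share needed for 60.** Without the survival factor, 60/75 = 0.80 (160 of the 200 a year), or 60/100 = 0.60 (120 of the 200) with the full look-back. With the survival factor, the look-back version needs 60/60 = 1.00. The version without look-back cannot reach 60, because 45e is at most 45.

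**Step 6. Range over e (assumed values).**

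| e | With survival: 45e | With survival and look-back: 60e | No survival: 75e | No survival, with look-back: 100e |
|---|---|---|---|---|
| 1.0 | 45 | 60 | 75 | 100 |
| 0.8 | 36 | 48 | 60 | 80 |
| 0.6 | 27 | 36 | 45 | 60 |
| 0.5 | 22.5 | 30 | 37.5 | 50 |
| 0.4 | 18 | 24 | 30 | 40 |
| 0.2 | 9 | 12 | 15 | 20 |

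In every column, accrual is proportional to e, and e is the factor that the plan omits.

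**The case against.** **The 200 may be new cases.** The article does not say whether it counts all women on treatment in a year or women starting treatment. The full protocol, which is not shown, may define it. This stands. It does not remove the point, because performance status, age, language and contraindications would still be unapplied.

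**The survival factor pulls the other way.** Since it is not an entry criterion, including it lowers the recruitment figure and may offset the missing eligibility factor. This also stands. If at least 80% of the 200 are eligible, or 60% with the full look-back, then 60 in 9 months is attainable.

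**The consequence is limited.** The size was set empirically and no error rate or power rests on it. Women are screened weekly at the center's board, and acceptance among eligible patients will be estimated, so the trial should produce better figures than its projection. The Results section reports a start in October 2016 and completed follow-up in January 2018. That is about 15 months, compatible with 9 months of recruitment plus 6 of follow-up, though it does not show how many women enrolled. All of this stands and keeps the point modest.

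**A stronger reading that the article does not support.** A reader might infer that most of the 200 were diagnosed in earlier years, and that the shortfall can be calculated. For example, a constant hazard fitted to 60% six-month survival is −ln(0.6)/0.5 = 1.022 per year, a mean of 0.98 years. In a steady state this gives 200/1.98, or about 101 new diagnoses a year, and 101 × 0.50 × 0.75, or about 38 acceptors in 9 months. That requires a constant hazard, a steady state, and treatment at this center until death, none of which the article states. Longer assumed mean survival would lower the figure but contradicts the plan's own input: under the same model, means of 1.5 and 3 years imply six-month survival of exp(−0.5/1.5) = 72% and exp(−0.5/3) = 85%, not 60%.

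**Conclusion.** The point holds as a mismatch between the base of the projection and the entry criteria. On the plan's own three factors, nine-month accrual is 45e, or at most 60e with the look-back, and so is below 60 for any eligible share below 1. Given the list of criteria, a share of exactly 1 is hard to defend.

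The projection cannot be called unattainable. Without the survival factor, accrual is 75e to 100e, and 60 is reached if e is at least 0.80 (0.60 with the full look-back). The size of the overstatement, and whether there is one once survival is removed, cannot be settled from the article, because it gives neither e nor the definition of the 200. The results assume even accrual over the year and the stated 50% acceptance. The consequence is confined to the stated accrual and any planning that reuses it. No power or inference is affected.

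**What to change.** Rewrite the projection in the Sample Size paragraph:

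1. State what the 200 counts: all women treated in a year, or new metastatic diagnoses.
2. Start from the annual number of newly diagnosed, otherwise eligible women seen at the weekly board. If only the 200 is available, give the eligible share applied to it and its source.
3. Multiply by acceptance among eligible women and scale to the recruitment period, saying whether women diagnosed in the 3 months before opening are counted.
4. Use the 60% survival factor only to derive the number expected to be evaluable at month 6.
5. Restate the expected number or the recruitment period to match.

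The cost is one reworded paragraph, with no change to the conduct or analysis of the trial. The downside is that the stated accrual may become less favourable. For planning the later multicenter trial, the observed screening and acceptance figures should replace the projection.

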#### Statistical Methods

Patients’ characteristics will be described at D1 and M6 using the mean and SD for quantitative data, frequency, and percentage for qualitative data.

The primary outcome to assess the feasibility of the study will be the proportion of patients achieving the physical activity recommendations corresponding to 150 minutes per week of moderate physical activity evaluated by the IPAQ score during the last week of the study. In addition, we will estimate the proportion of patients who agreed to participate in the ABLE Trial among eligible patients. The reasons for refusal will be documented and described as well.

The secondary outcomes to assess will be the evolution of physical activity, anthropometric, physical fitness, psychological, and biological variables between the initiation (D1) and the completion (M6) of the physical activity intervention using Wilcoxon signed-rank tests. In addition, the level of physical activity according to biological, psychological, and clinical outcomes adjusted on potential confounders, including age, treatment, and number of visits, will be explored using multiple linear regressions. Moreover, the level of oxidative stress will be correlated to the RECIST criteria. Data on barriers and facilitators of the adherence to a physical activity program from D1 to M6 will be compared by Mac Nemar tests. All statistical analyses will be performed using SAS software (version 9.4. SAS Institute Inc, Cary, NC, USA).

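### The Sample Size paragraph attaches a 12-month product to a 9-month period (its inputs give 45 in 9 months, not 60) and uses six-month survival as an enrolment factor

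*Protocol article*

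**What the plan says.** The Sample Size section of the protocol article states that "The sample size was defined empirically to explore the feasibility of the program according to the enrollment potential in the study center", and that "without major regard for the efficiency, no formal calculation was performed". It then gives the reasoning behind the target. "Given that 200 patients are treated annually for metastatic breast cancer in the Center Léon Bérard" is the starting pool, "60% of patients are expected to survive for at least 6 months" is the second factor, and the conclusion is that "with a projected acceptance rate of 50%, the pilot study will aim to recruit 60 patients within 9 months".

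Three other places bear on this:

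- The Methods part of the abstract describes a "single-arm trial with 60 patients who are newly diagnosed with metastatic breast cancer".
- Study Population requires patients to be "newly diagnosed with primary or secondary metastatic breast cancer histologically confirmed (ie, within the last 3 months" before enrolment, with a performance status below 2, an age of 18 to 78 years, no untreated brain metastases and no contraindication to physical activity. It lists no life-expectancy criterion.
- Statistical Methods defines the primary outcome as the proportion reaching "150 minutes per week of moderate physical activity evaluated by the IPAQ score during the last week of the study". It is therefore measured at the end of the six months.

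**The concern.** Two things in the Sample Size paragraph do not fit together.

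The first is the time unit. The pool is an annual count, but the target is set for 9 months. The product of the three inputs equals the target exactly only if the period is a full year, which suggests that the annual figure was carried over without scaling.

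The second is the role of survival. Whether a patient will live six months is not known when she is approached, and nothing in the eligibility criteria selects on it. Six-month survival therefore does not reduce the number who can be recruited. It reduces the number in whom an outcome at month 6 can be observed, and the paragraph says nothing about that number.

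What is at stake is planning information. The Discussion says that the results will help design a multicenter randomized trial. A planner who took this paragraph at face value would carry forward an accrual rate that its inputs do not give, with no allowance for deaths between enrolment and the primary outcome.

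**Working it through.** **Inputs, all from Sample Size:** pool 200 per 12 months; six-month survival 0.60; acceptance 0.50; target 60; period 9 months.

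**1. Reproducing the stated figure.**

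- Over 12 months: 200 x 0.60 x 0.50 = 60. This matches the target but not the period.
- Over 9 months: 60 x 9/12 = 45. This is 15 below the target, and 15/60 = 25%.

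**2. What 60 in 9 months would need with survival kept as a factor.**

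- Acceptance: 60 / (200 x 0.75 x 0.60) = 60/90 = 66.7%, against the stated 50%.
- Or annual pool: 60 / (0.75 x 0.60 x 0.50) = 60/0.225 = about 267, against the stated 200.

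**3. Survival removed from the enrolment product.**

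- Over 9 months: 200 x 9/12 x 0.50 = 75.
- Acceptance needed for 60: 60 / (200 x 0.75) = 40%.

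Under this reading 60 in 9 months is attainable, but the product is 75, so the stated figure is still not what the inputs yield.

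**4. Month-6 availability under the reading in step 3 only.** The paragraph's 60% has not been used at enrolment, so it applies afterwards.

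- At the stated rate: 60 x 0.60 = 36 alive at month 6.
- Assumed better survival among those enrolled: 60 x 0.70 = 42; 60 x 0.80 = 48; 60 x 0.90 = 54.

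These are counts of patients alive. Withdrawals and missing questionnaires would lower the number with an outcome.

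**5. Effect on precision, same reading.** The 95% half-width for a proportion near 50% is 1.96 x sqrt(0.25/n).

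- n = 60: 1.96 x sqrt(0.25/60) = 12.7 percentage points.
- n = 36: 1.96 x sqrt(0.25/36) = 16.3 percentage points.

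The second value applies only if the analysis is restricted to those 36. If patients without a month-6 assessment stay in the denominator as not achieving the recommendation, n remains 60.

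**6. Could the 9 months be a slip for 12?** The Results section puts the start of recruitment in October 2016 and the completion of follow-up in January 2018, at most 16 months. Taking off the six-month intervention leaves at most about 10 months for enrolment. At 60 per year, 10 months gives 60 x 10/12 = 50. The short window appears to be real, so changing 9 to 12 in the text would not by itself describe the trial.

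**7. Could a backlog explain it?** If patients diagnosed in the 3 months before opening were counted, 9 months of recruitment would cover 12 months of diagnoses, and 200 x 0.60 x 0.50 x 12/12 = 60. The article does not say this, and it would require all 200 patients treated annually to be newly diagnosed.

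**The case against.** The strongest reply is that nothing formal depends on this product. The article calls the sample size empirical, makes no power claim and sets no recruitment threshold. Its recruitment-related result is the proportion who agree among eligible patients, which does not depend on the 60, the 9 months or the 200. All of that stands, and it limits the severity.

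A reader might go further than the documents allow in three ways.

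- **Combining the two numbers.** It is tempting to say that only 45 can be recruited in 9 months and also that 60 recruited leaves only 36. These belong to exclusive readings. The 45 spends the 60% at enrolment; the 36 spends it afterwards. Once survival is treated as attrition, the inputs support 75 in 9 months and the recruitment shortfall disappears.
- **Saying that the month-6 number is overstated.** The article never states an expected number with month-6 data, so there is no figure to overstate. The gap is that the survival rate is given but not applied where it matters.
- **Taking 36 as firm.** The 60% describes patients treated at the centre. Those enrolled must have a performance status below 2 and medical clearance, and the article gives no survival rate for that group. Hence the range of 42 to 54 alongside 36.

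It can also be said that precision and loss allowances are commonly left to the full protocol or analysis plan. That is fair as to their absence, and their absence is not the point here. The article does print the survival rate and puts it in the wrong place.

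**Conclusion.** The point holds as a wrong planning figure. The stated inputs give 60 patients in 12 months or 45 in 9, so the target of 60 in 9 months does not follow from them; the gap is 15 patients, or 25%. This part rests on the article's own numbers and on even accrual over the year.

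Six-month survival is also misplaced: no eligibility criterion selects on it, and it bears on observation at month 6. With survival moved there, 60 in 9 months is attainable, and about 36 of the 60 would be alive at month 6 at the stated rate. That count assumes that the all-patient 60% applies to those enrolled.

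One further caution applies under either reading. The 200 patients treated annually are not the newly diagnosed eligible pool, and the documents do not give the size of that pool.

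Severity is minor to moderate. No power claim, analysis or decision rule changes.

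**What to change.** Restate the recruitment sentence in Sample Size under one reading:

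- **(a) Survival kept as a filter.** Give 45 patients in 9 months (60 in 12), say what the 60% stands for at enrolment, and do not apply it again to those recruited. If this is chosen, reconcile the period with the dates in Results.
- **(b) Survival removed from the enrolment product.** Give 200 x 9/12 x 0.50 = 75, note that 60 in 9 months then needs only 40% acceptance, and state that about 36 of 60 would be alive at month 6 at the stated 60% (42 to 54 at an assumed 70% to 90%). State the half-width with its denominator: about 16.3 points if only those 36 are analysed, 12.7 if all 60 are kept.

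Reading (b) fits the eligibility criteria and the timing of the primary outcome better. Under either, say that the 200 are all patients treated and, if the centre has the figure, replace it with the number meeting the entry criteria.

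The cost is a few sentences. No extra patients, data or analyses are needed. Since the article reports recruitment and follow-up as finished, the correction serves the report and the planning of the next trial.
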